**Fig. 1 Fig1:**
[figure not shown]
Flow diagram showing home-based exercise program for children with CHD following interventional cardiac catheterization

The intervention group will implement a home-based exercise program, while the control group will receive home-based exercise education. Both groups will continue with their routine activities, but they will not be able to attend any other formal exercise program.

This study design follows the SPIRIT guidelines (see Fig. 2 and Additional files 1 and 2).

**Fig. 2 Fig2:**
[figure not shown]
Time schedule of enrollment, assessments, and interventions

### Participants

#### Inclusion criteria

Children will be selected to participate in this study according to the following inclusion criteria: (1) echocardiography diagnosis of simple CHD with patent ductus arteriosus, pulmonary stenosis, ventricular septal defect, or atrial septal defect; (2) age 0 to 5 years; and (3) planned to undergo cardiac catheterization.

#### Exclusion criteria

Children will be excluded from participation in this study according to the following exclusion criteria: (1) arrhythmia; (2) CHD combined with other genetic disorders; (3) other congenital deformities; (4) liver or kidney diseases; (5) heart failure with a modified Ross score of 3 points or more; (6) history of heart surgery except cardiac catheterization; (7) operation on other organs; (8) previous rehabilitation treatment; (9) illnesses that may preclude the child from participation in the study as identified by the study physician.

### Withdrawal criteria and management

Children with CHD and their families will be allowed or be asked to withdraw from the study in the event of the following:The child and his/her family make such a request.The child has an adverse effect/event related to participation in the study.

### Intervention

The home-based exercise program will consist of home-based exercise education, home-based exercise, and home-based exercise supervision.Home-based exercise education: The intervention team will explain the results of the developmental tests of their children to each family and emphasize the importance of home-based exercise for their children. Then, parents will receive a home-based physical activity brochure, and follow a Micro Message Public Platform that will share various forms of CHD knowledge twice monthly including exercise, education materials, and general care of children with CHD. It will also provide the exercise guide and tools for outpatient appointments. Parents will be asked to take their children to perform daily outdoor activities.Home-based exercise: The home-based exercise program will be adopted from the motor activities program of Peabody Motor Development [27]. The home-based exercise program will be designed by the pediatric cardiologist, rehabilitation physician, and intervention team with input from the parents. The home-based exercise program will be individualized to each child’s developmental age, severity, and degree of developmental delay. The baseline assessment results will be used to identify age-appropriate skills that the children have not yet mastered. The exercise program will be designed so that parents can choose how to incorporate these activities into their daily schedules and preferred behaviors. First, a member of the intervention team will provide the parents with one-on-one rehabilitation program training until the parents master the skills. In addition, the parents will be given a home-based game reader and the Micro Message Public Platform to guide them. At least one of the children’s parents will be asked to complete the entire exercise program, and the rest of the family members must agree and support the home-based exercise program. The intervention team will maintain contact with the parents by phone to provide the exercise guide.

#### Outline of the home-based exercise program

The outline of the home-based exercise program will differ by developmental age:Age 0–6 months Developmental activities: activities/games with different postures, such as head lifting, support in prone position, hand, or elbow support, etc. For example, the infant could lie on the mother’s leg in a prone position; the mother could shake a soundtoy over the infant’s head to induce the infant to lift his/her head or hand; the infant can also lie on a big ball in a prone position Passive exercise: stretching the infant’s limbs and shoulder, and wrist and leg manipulation by the parents, such as clapping or nudging the infant’s feet.

*Parents will implement the rehabilitation program at home over a 6-month period; the total daily time request will be 30 minutes for no less than 5 days per week.*
Age 7–12 months Developmental activities: activities in different positions (prone, sitting, crawling, creeping, kneeling, and standing) Passive exercise: stretching the infant’s limbs and shoulder, and wrist and leg manipulation by the parents, like the baby’s feet touching the mother’s feet with bending and extending movements, and stepping on a bicycle.

*Parents will implement the rehabilitation program at home over a 6-month period; the total daily time request will be 30 minutes for no less than 5 days per week.*
13–24 months Postural training: kneeling and standing Flexibility training: active stretching of the upper and lower limbs, chest expansion, and shoulder, wrist, and leg movement Breathing exercises: abdominal respiration, resisted breathing, deep breathing, and blowing bubbles and pinwheels Developmental activities: walking, stair activities, stepping activities, and throwing a ball Aerobic endurance training: swimming, riding a bike, and walking.

*Parents will implement the rehabilitation program at home over a 6-month period; the total daily time request will be 30 minutes for no less than 5 days per week.*
25–60 months Postural training: single-leg standing, standing on tiptoe, single-leg jumping, such as jumping following a rope with snake shapes, rope skipping, or standing on a soft cushion Flexibility training: active stretching of the upper and lower limbs, chest expansions, and shoulder, wrist, and leg movements Breathing training: abdominal respiration, resistant breathing, deep breathing, and blowing bubbles and pinwheels Muscle strength training: pulling elastic bands with the upper limbs, squatting down and standing up, straight-leg raising movements, and gluteus training, like hiding in a big box, and inducing the child out with preferred toys Developmental activities: climbing upstairs and coming downstairs, stepping activities, and throwing and kicking a ball Aerobic endurance training: swimming, riding a bike, walking, jogging, and running to catch things with a crossing obstacle.

*Parents will implement the rehabilitation program at home over a 6-month period; the total daily time request will be 30 minutes for no less than 5 days per week.*

#### Safety supervision of home-based exercise training

Researchers will provide a portable device to parents that can be used to detect the blood oxygen saturation and heart rates of children with CHD. The heart rates of children with CHD will be maintained in a targeted range (60–80% of maximum heart rate) throughout the training. The training will stop if the child exceeds the maximum heart rate. The maximum heart rate will be calculated by a physiatrist according to the child’s age.

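### One 60–80% of maximum heart-rate range covers every part of the session at every age, including passive, stretching and breathing work, and the only explicit action is a stop above 100%

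*Protocol article*

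**What the plan says.** The section on safety supervision of home-based exercise training gives parents a "portable device to parents that can be used to detect the blood oxygen saturation and heart rates of children with CHD". It then sets the target: "The heart rates of children with CHD will be maintained in a targeted range (60–80% of maximum heart rate) throughout the training". The one action it names is: "The training will stop if the child exceeds the maximum heart rate". A physiatrist calculates the maximum from the child's age; no formula or value is given, and no saturation threshold is stated.

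The outline of the exercise program assigns components to four age bands. The same dose applies to each: "the total daily time request will be 30 minutes for no less than 5 days per week". The components differ widely in effort. At 0–6 months the passive item includes "wrist and leg manipulation by the parents, such as clapping or nudging" of the feet. At 7–12 months the active item is "Developmental activities: activities in different positions (prone, sitting, crawling, creeping, kneeling, and standing". At 13–24 months the list includes "Breathing exercises: abdominal respiration, resisted breathing, deep breathing, and blowing bubbles and pinwheels", and the 25–60 month band has a near-identical breathing item. Parents deliver all of this at home, after "one-on-one rehabilitation program training until the parents master the skills".

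**The concern.** A target zone with a lower and an upper limit suits exertional exercise. Here it is written for the whole session and for all children aged 0 to 5 years, although part of every band's program is a parent moving an infant's limbs, stretching, or blowing bubbles. For those parts a minimum heart rate serves no visible aim, and a parent who takes it literally could be led to ask for more effort than the activity is meant to involve.

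The upper side matters more for safety. A parent watching a device needs to know at what reading to intervene and what to do. The article gives a target that ends at 80% and a stop that begins above 100%, with no written step between them. At stake is how clear and how early the in-session safety instruction is, not any result of the trial.

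**Working it through.** There is no sample-size, power or error-rate figure to reproduce. The check is a count of labelled components and a comparison of the rule with the activities it governs.

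**Step 1: components per age band** (outline of the home-based exercise program).

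| Age band | Components listed | Passive, flexibility or breathing | Share | Labelled aerobic |
|---|---|---|---|---|
| 0–6 months | 2 (developmental, passive) | 1 | 1/2 = 50% | 0 |
| 7–12 months | 2 (developmental, passive) | 1 | 1/2 = 50% | 0 |
| 13–24 months | 5 (postural, flexibility, breathing, developmental, aerobic) | 2 | 2/5 = 40% | 1 |
| 25–60 months | 6 (postural, flexibility, breathing, strength, developmental, aerobic) | 2 | 2/6 = 33% | 1 |

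Summed over bands this is 6 of 15. No child is assigned all 15, so the band shares are the figures to use.

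**Step 2: time under the rule.** 30 minutes × 5 days = at least 150 minutes a week. No minutes per component are given, so the share of that time spent in the low-exertion components is unknown.

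**Step 3: the rule by heart-rate zone** (safety supervision section).

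| Zone, % of maximum | What is written |
|---|---|
| Below 60 | Outside the target; no action stated |
| 60 to 80 | Target, for the whole session |
| Above 80, up to 100 | Outside the target; easing off implied, no action stated |
| Above 100 | Stop |

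The zone between the ceiling and the stop is 100 − 80 = 20% of maximum.

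**Step 4: scale in beats per minute, as an assumption.** The article gives no maximum. For assumed maxima of 180 to 220 beats/min:
- floor: 0.6 × 180 = 108 to 0.6 × 220 = 132
- ceiling: 0.8 × 180 = 144 to 0.8 × 220 = 176
- ceiling to stop: 180 − 144 = 36 to 220 − 176 = 44 beats/min

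**Step 5: does the floor do anything in low-exertion work?** If a child's resting rate is well below 60% of maximum, passive or breathing work may leave the child under the floor, and the wording then asks for more effort. If the resting rate is already near or above 60%, as it may be in infants, the floor prescribes nothing. The article does not say which case applies. In neither case does the floor serve these components.

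**Step 6: how late is the stop?** It acts only above the age-calculated maximum. If that value is close to the child's true maximum, the stop will seldom or never be reached. The only usable upper limit is then 80%, and no instruction is attached to it.

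**The case against.** Several counter-arguments carry weight.

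- *Keeping the rate within a range already tells the parent to bring it down above 80%.* This stands. A reader might infer that nothing is required of the parent between 80% and 100%; the text does not support that. What is unwritten is the form of the response: slow down, pause or rest.
- *The floor may be harmless.* This also stands. A reader might infer that the floor cannot govern whole sessions, or that it drives infants to over-exertion. Either claim needs resting and maximum heart rates, which the article does not give. The labels are also an imperfect guide to effort: the flexibility work from 13 months is active stretching, and the breathing work includes a resisted form.
- *Step-by-step instructions belong in materials not shown.* The article mentions a brochure, a game reader, platform guidance, phone contact and individual training, and the program is designed with a cardiologist and a rehabilitation physician and tailored to each child. Details of the response above 80% may well be there, so their absence from the article is not an error in itself. The scope of the range and the level of the stop, however, are stated in the article, and added detail would have to contradict the stated scope to narrow it.
- *The children are at low risk.* They have simple CHD, and arrhythmia or a modified Ross score of 3 or more excludes them. This limits the severity but does not make the rule fit the activities.
- *The range stands under a safety heading, so it is mainly a ceiling.* That is plausible, and it is a reason to write it as one.

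**Conclusion.** The point holds in a limited form. The article applies a 60–80% range to the whole session in every age band, although between 33% and 50% of each band's listed components are passive, flexibility or breathing work that has no evident need of a lower limit. The only explicit heart-rate action comes above 100% of the calculated maximum, 20% of maximum above the top of the target, which is late for parent-supervised home exercise after catheterization.

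The counts and zone limits come directly from the article. That the floor has no purpose in these components is a judgement from their labels. Whether it would bind is unknown and is not claimed. The beats-per-minute figures rest on an assumed maximum of 180 to 220. Severity is minor: this is safety and delivery wording, with no effect on sample size, outcomes or analysis.

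**What to change.** Three changes to the safety supervision section, repeated in the parents' materials:

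1. Replace the closing words that extend the range to the whole session, so that the 60% lower limit does not apply to passive, stretching and breathing work.
2. Make 80% of maximum, or a lower age-specific value set by the physiatrist, the upper limit for all components, and state the action: on reaching it, the parent pauses and lets the child rest.
3. Keep the existing stop above maximum.

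Nothing further is needed. An age cut-off for the target, or a list of which active components must reach it, would be a clinical choice for which the article gives no basis.

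The cost is a wording amendment, a narrower statement of prescribed intensity and some extra pauses during sessions. No statistical element changes.

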#### Compliance supervision

The intervention team will remind parents to carry out the exercise program and monitor each child’s progress through a Micro Message Public Platform or phone call one or two times weekly, and will also help them schedule rehabilitation evaluation appointments.

### Control group

The intervention team will explain the children’s evaluation results and share home-based exercise education with parents at baseline assessments. Home-based physical activity education will be given to the parents, but they will not receive the rehabilitation guide.

### Outcome measures

All assessments will be undertaken before the procedure and at 1, 3, and 6 months after the procedure.

### Primary outcome measures

#### Motor ability quotient

The Peabody Developmental Motor Scales, 2nd edition (PDMS-2) [28] will be used to assess each child’s motor development. The PDMS-2 is a performance-based tool used to assess motor development in both clinical and research settings. The PDMS-2 measures development in two domains, gross motor and fine motor, and it incorporates both quantitative and qualitative rating criteria. It consists of six sub-tests: reflexes, stationary, locomotion, object manipulation, grasping, and visual-motor integration. Sub-test scores are standardized by age and combined to calculate gross, fine, and total motor quotients. The raw scores for each of the sub-tests will be converted to age-equivalent scores, percentile ranks, standard scores, and composite scores. The PDMS-2 is a valid and reliable tool to assess motor development in children, and has excellent intra-rater reliability.

### Secondary outcome measurements

#### Ross score

The Modified Ross Heart Failure Classification will be used to assess children’s cardiac functions [29]. It is used to assess the cardiac functioning of children aged 0–14 years, including their history (diaphoresis, tachypnea) and physical examination (respiratory rate, heart rate, hepatomegaly size); the total scores range from 0 to 12 as follows: 0–2 (no congestive heart failure), 3–6 (mild congestive heart failure), 7–9 (moderate congestive heart failure), and 10–12 (severe congestive heart failure).

#### Index of echocardiography

The left ventricular diastolic diameter, left ventricular systolic diameter, and left ventricular wall thickness will be measured before and after the procedure to monitor the inner diameter changes in cardiac chamber. Function change of left and right ventricles, pulmonary artery systolic pressure, and pulmonary valve pressure difference will also be tested. The left ventricular end-systolic volume, left ventricular end-diastolic volume, and left ventricular short axis shortening rate are used to evaluate the left ventricular function. The tricuspid valve systolic peak velocity is used to check the right ventricular function. Measurements of highest velocity and defect size will be recorded before the procedure, and correct location and residual shunt will be verified by a cardiologist using echocardiography [4].

#### Speed of sound at the tibia

Speed of sound (SOS) will be evaluated using Quantitative Ultrasound measurements (Sunlight Omnisense TM7000, Petah Tikva, Israel) by the same trained rehabilitation physician. Each subject is seated close to the examination table and the patient’s non-dominant leg is rested. After introducing the water-soluble coupling gel, the probe moves across the tibia plane, searching for the site with a maximal reading. The measurement site is defined as the distal one-third of the tibia. The SOS is influenced by the bone minerals (major factor), bone thickness, microstructure, and skeletal elasticity [30].

#### Functional independence level

The WeeFIM (functional independence measure) instrument is a useful pediatric functional independence assessment tool for children aged 6 months to 7 years and for children with developmental disabilities aged 6 months to 21 years. It is an 18-item, 3-domain questionnaire that measures a child’s consistent performance in essential daily functional skills. Three main domains (self-care, mobility, and cognition) are assessed by interviewing or by observing a child’s performance of a task to criterion standards. Each item is rated on a 7-point ordinal scale ranging from 7 (complete independence) to 1 (total assistance). The WeeFIM is a psychometrically sound instrument in terms of its reliability, validity, and responsiveness [31]. Studies have already demonstrated that the WeeFIM can be used as a functional independence measure for Chinese children [32].

#### Anxiety

The Self-Rating Anxiety Sale (SAS) will be used to assess parents’ anxiety status. The SAS is a popular subject scale to measure anxiety. It has 20 items, scored as 1, 2, 3, or 4. Lower total scores mean lower anxiety: <50 (no anxiety); 51–60 (mild anxiety); 61–70 (moderate anxiety); >70 (severe anxiety) [33].

#### Quality of life

The Short Form 36 (SF-36) is used to evaluate parents’ quality of life; it is a widely used health status survey designed to assess quality of life by measuring the individual’s self-perception of his/her own health status with 8 multi-item scales, including physical functioning, physical role functioning, bodily pain, general health, vitality, social functioning, emotional role functioning, and mental health, and one single item of health transition. It can be used to assess the quality of life for patients with various diseases or people in general. The reliability, validity, and sensitivity of the Chinese (simple) SF-36v2 have been verified [34].

#### Caregiver burden

The Zarit Caregiver Burden Scale (ZCBS) is a widely used and valued assessment tool for caregiver burden, which was designed in line with Zarit’s Caregiver Burden measurement theory [35]. The ZCBS has two dimensions: personal strain and role strain, with a total of 22 items. Each item is rated on a 4-point scale, and higher scores represent a more serious burden: 0–20 (little or no burden); 21–40 (mild to moderate burden); 41–60 (moderate to severe burden); 61–88 (severe burden), corresponding to the subjective feeling.

### Sample measurement

GPower 3.1.9.2 will be used to perform the power calculations. The motor quotient of the PDMS-2 will be our primary outcome measurement.

The results of our pilot study showed that after 6 months of intervention, the motor quotient of the intervention group with patent ductus arteriosus on average was (94.33 ± 11.29), and that of the control group was (84.67 ± 6.11); therefore, the effect size was 1.06. Thus, as the α will be 0.05 and the β will be 0.05, each group should recruit 24 patients. Considering 10% potential attrition, 27 patients in each group with patent ductus arteriosus will be recruited.

The motor quotient of the intervention group with pulmonary stenosis on average after 6 months of intervention was (101.00 ± 9.90), and that of the control group was (89.00 ± 1.41); therefore, the effect size was 1.70. Thus, as the α will be 0.05 and the β will be 0.05, each group should recruit 11 patients. Considering 10% potential attrition, 13 patients in each group with pulmonary stenosis will be recruited.

The motor quotient of the intervention group with ventricular septal defect on average after 6 months of intervention was (95.00 ± 8.54), and that of the control group was (90.50 ± 7.78); therefore, the effect size was 0.55. Thus, as the α will be 0.05 and the β will be 0.05, each group should recruit 87 patients. Considering 10% potential attrition, 96 patients in each group with ventricular septal defect will be recruited.

The motor quotient of the intervention group with atrial septal defect on average after 6 months of intervention was (99.67 ± 5.43), and that of the control group was (90.80 ± 5.72); therefore, the effect size was 1.59. Thus, as the α will be 0.05 and the β will be 0.05, each group should recruit 12 patients. Considering 10% potential attrition, 14 patients in each group with atrial septal defect will be recruited.

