**Methods/design:**

A total of 300 children who will perform a cardiac catheterization will be randomly assigned to two groups: a home-based intervention group and a control group. The home-based intervention group will carry out a home-based exercise program, and the control group will receive only home-based exercise education. Assessments will be undertaken before catheterization and at 1, 3, and 6 months after catheterization. Motor ability quotients will be assessed as the primary outcomes. The modified Ross score, cardiac function, speed of sound at the tibia, functional independence of the children, anxiety, quality of life, and caregiver burden of their parents or the main caregivers will be the secondary outcome measurements.

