### Study design

Children with CHD who are planning to perform a cardiac catheterization procedure will be recruited from the Department of Pediatric Cardiology, Xinhua Hospital affiliated to Shanghai Jiao Tong University School of Medicine, China.

The study will be implemented at the Shanghai Jiao Tong University School of Medicine. Before participation in the study, parents/legal guardians will be asked to sign a written informed consent. First, patients who meet the inclusion criteria will be recruited for the study through echocardiography results. Second, patients will undergo baseline evaluations including motor abilities, cardiac function, modified Ross score, sound of speed at the tibia, and functional independence level, and their parents will complete three questionnaires about their anxiety levels, quality of life, and caregivers’ burden. Children with CHD will be allocated by a physician using computer-generated block randomization into two groups: an intervention group and a control group after the catheterization process. The allocations will be concealed in sequentially numbered, opaque, sealed envelopes through a signature across the sealing point. A trained research assistant, who will be blinded to the allocation, will enroll patients and assign them to interventions. All evaluations will be carried out by the evaluation team. Another team, composed of experienced pediatric physiotherapists, will teach parents the home-based exercises, remind them to perform the exercises, and provide valuable information about the details of the exercises. The evaluation team will be blinded in this program; however, the intervention team will not be blinded, as they must communicate with parents and offer informed consent in order to obtain the parents’ signatures. The intervention group will receive a home-based exercise program, while the control group will only receive home-based education (see Fig. 1). All children and parents will be evaluated by the trained evaluation team before the procedure and 1, 3, and 6 months after the cardiac catheterization. Micro Message Public Platform dissemination and collaboration with staff of the Department of Pediatric Cardiology was established to facilitate enrollment to reach the target sample size. All parents will be added into a CHD group of the Micro Message Platform created by the intervention team to remind them to bring their children for clinic visits in order to promote patient retention.

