### Data collection, management, and analysis

Data will be entered using EpiData software designed for this study. All data will be collected, typed, and analyzed by a statistician, who will be blinded during the trial. The main investigators will check the data every 2 weeks to ensure the quality. All statistical analyses will be performed using SPSS 20.0. Descriptive data will be presented as mean ± standard deviation. Considering that age may be a potential factor influencing the outcome measurement, a covariance analysis will be used to compare the effects between two groups. A *t* test will be used to compare changes in parent outcome measures in the two groups. Multiple linear mixed models will be used to analyze the relationships between the risk factors and the outcome measures. An intention-to-treat analysis will be used if participants are lost to follow-up. All statistical tests will be performed at a significance level of 0.05.

The parents will also be informed of this crucial aspect, and a member of the intervention team will be available any time the parents may need further information or clarification during the study period.

An interim analysis will be performed by the statistician on the primary endpoint; the statistician will be blinded for treatment allocation and will report to the main investigators. The main investigators will discuss the results of the interim analysis with the monitoring board. However, the trial will be terminated in case of harm. The criterion for stopping the trial for harm is as follows: a statistically significant difference in the primary outcome between the intervention group and a reasonable suspected causal relationship between the intervention and adverse events.

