### Strengths and limitations

The first strength of our study is that it will be the first randomized controlled trial that focuses on home-based exercise for young children with CHD and cardiac catheterization. Second, except for the important elements of cardiac function, our study focuses more on growth development at an early stage for children with CHD. Third, we used GPower 3.1.9.2 software for the sample calculation to ensure its scientific validity. Fourth, our study will last for 6 months, with three re-evaluations, in order to update the patients’ recovery and development status in time. Fifth, our study develops a detailed and individual home-based exercise program for each patient, and provides a one-on-one guide for the parents, until they master the skills. Moreover, there is a close home-based monitoring process, which could ensure the quality of implementation of the home-based exercise program to a certain extent. Sixth, our intervention will not solely focus on the children, as their parents will also be educated in home-based exercise and other appropriate educational and care guidelines for children with CHD.

Several limitations exist in our trial: (1) the age of subjects is limited to 0 to 5 years; (2) we only recruit patients with cardiac catheterization for our trial; we will not group the children according to their specific CHD subtypes or the treatment approach to CHD; (3) we will not evaluate language and speech development or cognitive development directly, only motor development; thus, our trial cannot be used as a comprehensive evaluation of all types of home-based exercise programs for CHD children with cardiac catheterization; and (4) our study includes a short follow-up duration of 6 months.

In conclusion, our study design for delayed motor development of CHD children with cardiac catheterization developed a home-based exercise program as the main intervention approach after the procedure. It is crucial to address whether a home-based exercise program could improve the patients’ motor abilities and improve parental anxiety, burden, and quality of life. The findings will be beneficial for children with CHD and their families, research collaborators, physicians, and the general public.

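### The 300 children come from four lesion-specific calculations at 95% power, but the article disclaims grouping by lesion and states no power for the pooled comparison it describes

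*Protocol article*

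**What the plan says.** The Sample measurement section of the protocol article works through four lesions in turn: patent ductus arteriosus, pulmonary stenosis, ventricular septal defect and atrial septal defect. Each has its own pilot means and SDs, its own effect size and the same error rates: "as the α will be 0.05 and the β will be 0.05". For ventricular septal defect the result is that "each group should recruit 87 patients. Considering 10% potential attrition, 96 patients in each group with ventricular septal defect will be recruited". The other lesions get 24, 11 and 12 evaluable children per arm, raised to 27, 13 and 14 for attrition.

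The abstract gives the overall size: "A total of 300 children who will perform a cardiac catheterization will be randomly assigned to two groups".

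Three other places bear on how those children will be used:

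- Study design: children are "allocated by a physician using computer-generated block randomization into two groups". No lesion strata are mentioned.
- Data collection, management, and analysis: with age given as the reason for adjustment, "a covariance analysis will be used to compare the effects between two groups". No lesion term or lesion-specific test is mentioned.
- Strengths and limitations: "we will not group the children according to their specific CHD subtypes or the treatment approach to CHD".

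**The concern.** A sample-size statement should give the power of the test that will be used for inference. Here the only power statement concerns comparisons within each lesion, while the limitations section says that children will not be grouped that way and the analysis section compares two arms.

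Two things follow. A reader cannot tell from the article whether the primary inference is one test or four. And the within-lesion claims, left standing, invite efficacy conclusions from as few as 11 or 12 evaluable children per arm under a power label that no planned analysis carries. If four lesion tests at 0.05 were run after all, the familywise error would be about 18.5% (1 − 0.95⁴ = 0.1855, assuming independence), and the article gives no rule for controlling it.

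**Working it through.** **Inputs.** All are from the Sample measurement section, except the total of 300, which is in the abstract. The article does not state sidedness. Two-sided tests reproduce its figures; one-sided tests (20, 9, 73 and 10 per arm) do not.

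**Step 1: reproduce the plan's figures.** Effect size d = (mean₁ − mean₂) / √[(SD₁² + SD₂²)/2]. Evaluable n per arm is from the two-sample t test (noncentral t), two-sided 0.05, power 0.95.

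| Lesion | Difference | Average variance | d (stated) | Evaluable n per arm, recomputed (stated) | Recruited per arm (stated) |
|---|---|---|---|---|---|
| Patent ductus arteriosus | 94.33 − 84.67 = 9.66 | (11.29² + 6.11²)/2 = 82.40 | 1.064 (1.06) | 24 (24) | 27 |
| Pulmonary stenosis | 101.00 − 89.00 = 12.00 | (9.90² + 1.41²)/2 = 50.00 | 1.697 (1.70) | 11 (11) | 13 |
| Ventricular septal defect | 95.00 − 90.50 = 4.50 | (8.54² + 7.78²)/2 = 66.73 | 0.551 (0.55) | 87 (87) | 96 |
| Atrial septal defect | 99.67 − 90.80 = 8.87 | (5.43² + 5.72²)/2 = 31.10 | 1.590 (1.59) | 12 (12) | 14 |

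For patent ductus the unrounded d gives 24; the rounded 1.06 gives 25. For ventricular septal defect, 96 is 87 × 1.10 = 95.7 rounded up, while 87/0.90 = 96.7 would give 97. Neither difference matters here.

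**Step 2: where the 300 comes from.** Recruited per arm: 27 + 13 + 96 + 14 = 150, and 2 × 150 = 300. Evaluable per arm: 24 + 11 + 87 + 12 = 134. The total is exactly the sum of four separate designs.

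**Step 3: the effect in the pooled comparison, on the pilot's own figures.** Weight each lesion by its evaluable n.

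- Difference: (24 × 9.66 + 11 × 12.00 + 87 × 4.50 + 12 × 8.87)/134 = 861.78/134 = 6.43 points.
- Within-lesion SD: √[(24 × 82.40 + 11 × 50.00 + 87 × 66.73 + 12 × 31.10)/134] = √64.97 = 8.06, so d = 6.43/8.06 = 0.80. This corresponds to a model with lesion as a factor.
- SD including the spread of means between lesions: about 8.35, so d = 6.43/8.35 = 0.77. This corresponds to a model without lesion.

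**Step 4: power of the pooled comparison.** Two-sided 0.05, 134 per arm, 266 degrees of freedom, noncentrality d × √(134/2).

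| Assumed d | Noncentrality | Power |
|---|---|---|
| 0.55 (smallest lesion effect in the pilot) | 4.50 | 99.4% |
| 0.77 | 6.30 | over 99.9% |
| 0.80 | 6.55 | over 99.9% |
| 0.442 | 3.62 | 95% |

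The effect detectable with 95% power is therefore about 0.44 SD, or 0.442 × 8.06 = 3.6 to 0.442 × 8.35 = 3.7 motor-quotient points.

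**The case against.** The strongest reply is that nothing is lost. The arithmetic is right, the pooled test has ample power, and the mismatch neither biases the pooled estimate nor inflates its type I error. All of that stands. It limits the point to a contradiction between sections and an unstated power.

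A second reply is that the article condenses a fuller protocol, so lesion strata or a lesion covariate may be specified elsewhere, and the mixed models for risk factors could include lesion. This also stands in part: silence on strata in the Study design section does not show that allocation is unstratified. But the limitations section says affirmatively that children will not be grouped by subtype, and the sample-size section rests wholly on such grouping. An unseen document cannot reconcile those two statements as written. The mixed models are described for risk factors, not for the treatment comparison.

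A reader might also infer more than the documents support:

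- **The trial is underpowered, or its error rate is 18.5%.** The pooled test is not short of power, and the 18.5% arises only if four lesion tests are run, which the article does not plan.
- **Within-lesion power collapses.** Power of 43% in pulmonary stenosis (11 per arm), about 47% in atrial septal defect (12 per arm) and 77% in patent ductus (24 per arm) follows only if every lesion shares d = 0.80. That is an assumption; the article states 1.70, 1.59 and 1.06.
- **Lack of stratification undermines the lesion comparisons.** At the stated effects, averaging power over unstratified splits of the evaluable totals costs under one percentage point (for example 96.6% to 95.9% in pulmonary stenosis).
- **The pilot had two or three children per cell.** Some printed SDs suggest very small cells, but larger cells can give the same values, and the article does not state the pilot size.

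**Conclusion.** The point holds as an internal contradiction that should be fixed; it does not endanger the trial. The stated 95% power attaches to four lesion-specific tests that the article does not plan, and the power of the planned two-arm comparison is missing. On the pilot figures that power is between 99.4% and over 99.9% with 134 evaluable children per arm, so 300 is more than the pooled comparison needs for 95% power: about 45 evaluable per arm at d = 0.77, or 87 at d = 0.55.

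These figures assume two-sided 0.05, equal allocation, the planned lesion mix and attrition as stated, and an unadjusted t test as a stand-in for the covariance analysis. They take the pilot effects at face value. The 0.44 SD figure is solved from the sample size; it describes what the trial can detect and is not a minimum important difference, which the sample-size section does not give.

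**What to change.** Keep 300 and change the wording as follows.

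1. Restate the Sample measurement section for the single pooled comparison: 150 recruited and 134 evaluable per arm, two-sided 0.05, 95% power for about 0.44 SD, with 99.4% power at 0.55 SD and over 99.9% at 0.77 to 0.80 SD. The four lesion calculations can stay as background on how the number was reached.
2. Withdraw the claims of 95% power within each lesion.
3. Include lesion as a factor in the covariance model alongside age. The diagnosis is established at enrolment by echocardiography, so no new data are needed.
4. Report lesion-specific effects as descriptive estimates with intervals, optionally with one treatment-by-lesion interaction test.
5. Reconcile the Sample measurement section with the limitation on grouping by subtype, so that both describe the same primary inference.

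The cost is protocol wording and one model term, with no extra children. The downside is that the within-lesion power claim is given up. Moving to lesion-stratified allocation is not required: recruitment is already under way, the gain at the stated effects is small, and two allocation schemes in one trial would need their own justification.
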